### Safety and ethical issues

Research activities within the UBICA-TeeMo project will be carried out in compliance with the fundamental ethical principles as stated by the Declaration of Helsinki. The Coordination Centre for Clinical Trials (KKS) will monitor the study, adapted to ICH-GCP guidelines (E6), and has approved the standard operating procedures. The trial has received approval from the local Research Ethics Committee at the University Hospital RWTH Aachen (reference EK144/12, protocol version 2.0 to 7.0). Any modification to the protocol will require a formal amendment and approval by the local Research Ethics Committee. The protocol must be agreed on by the Trial Steering Committee (principle investigators at the Department of Child and Adolescent Psychiatry, University Hospital RWTH Aachen) and Data Management Team (KKS and IMBI) at the University of Heidelberg.

Participants will be enrolled only after they have received comprehensive information from the responsible investigator. Participants will also receive information sheets and will have the opportunity to discuss the trial with the investigator. Written informed consent for the study will be obtained by the investigator from all participants who are willing to participate in the trial. Additional consent is obtained from participants for collection of genetic and neuroimaging data. Infants will only be included if the adolescent or young adult mother and the guardian have both given informed consent. All participants will be informed that they can stop participating in the study at any time without giving any reasons. Furthermore, additional consent is obtained from all participants who are willing to be contacted by the trial investigator for their participation in ancillary studies.

Study participants are provided with the right to have their information removed from the database at any time. Trial results will be communicated to participants and healthcare professionals who were involved in the study. Results will be published regardless of the magnitude or direction of the effect.

An independent Data and Safety Monitoring Board (DSMB), including two independent clinical experts and one biometrician, is established to monitor the progress of the trial and ensure adherence to protocol. Safety parameters include that all serious adverse events (SAE) or adverse events reported by the subject or detected by the local investigator that occur during the trial and all noticeable problems must be documented in the case report form (CRF). In case of an SAE, the Ethics Committee and DSMB will be informed within 24 h after the SAE becomes known. In case of significant preponderance of SAEs that might causally be associated with the trial, the DSMC will terminate the trial. Patients that are enrolled in the study are covered by indemnity for negligent harm by study insurance policies. Substantive contributions to the design, conduct and interpretation of the trial are recognized through the granting of authorship on the final trial report.

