### Intervention: STEEP-b

The intervention (STEEP-b) is an adaptation of the STEEP program [35], which aims to enhance sensitive care using video-feedback to guide parents to recognize their children’s signals, take their children’s perspective and understand their children’s needs. STEEP-b was designed to be relatively brief, completed in 12 to 18 sessions, and started when the children are between 3 and 6 months of age (as a detailed meta-analysis could demonstrate [25], interventions with a small to moderate number of sessions and those with an older infant are more effective than longer interventions and those with very young infants). Adolescent mothers are visited at home every 2 to 3 weeks by the same adviser for 9 months. Furthermore, an optional group meeting is offered every second month that mothers can attend. The exact number of sessions will depend on clinical appropriateness in the 9-month window. The original STEEP program is not manualized; however, as treatment manualization is considered an important factor in treatment integrity and effectiveness [25, 36], STEEP-b has been modularized with every session focusing on one of four obligatory modules. The four modules emphasize the following elements: child development, maternal sensitivity, frightening and intrusive behaviors and sensitive discipline. Every module should be worked on twice, with the order depending on clinical appropriateness. A promising tool to increase sensitive parenting is video-feedback [25]. A study in adolescent mothers demonstrated positive maternal behaviors and improved affective scores after video feedback of mother-infant interaction, but not in a control group [37]. Therefore, video-feedback of free interaction situations and structured interaction situations will be used to work on the intervention topics. In addition, if the baseline assessment reveals any psychiatric diseases in the mother (for example, depression or PTSD), arrangements will be made for individual psychiatric treatment to be offered by a qualified clinical psychologist or psychiatrist within 4 weeks after the diagnostic assessments. The intervention is discontinued at the participant’s request or if interventions are no longer possible due to the separation of the mother and child (>3 months) or any other serious harm (severe illnesses of either mother or child, death of participants) preventing study participation. Whenever possible, study participants are retained in the trial to enable follow-up data collection and to prevent missing data. Participants who are assigned to the TAU arm are not allowed to receive any intervention using video-feedback.

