
### Measurement time points

The flow of participants from recruitment through the end of the study is shown in Fig. 1. Children and mothers will be systematically assessed at T1 (pre-intervention, child age 3 to 6 months), at the end of the 9-month intervention (T2, postintervention) and 6 months postintervention (T3, follow-up). Moderators of treatment outcomes and sociodemographic data will be assessed at T1. Concomitant care is documented at all measurement time points.

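### SAEs are captured passively while study contact differs between arms until T2, so an apparent STEEP-b excess can arise at equal true rates, mainly at interim looks

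*Protocol article*

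**What the plan says.** **Capture.** Under Safety and ethical issues, the events to be documented are "all serious adverse events (SAE) or adverse events reported by the subject or detected by the local investigator that occur during the trial". The wording is the same for both arms, and no scheduled safety enquiry is described. For an SAE, "the Ethics Committee and DSMB will be informed within 24 h after the SAE becomes known", so the clock runs from knowledge of the event and not from its onset.

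**Action.** The same section continues: "In case of significant preponderance of SAEs that might causally be associated with the trial, the DSMC will terminate the trial". It gives no threshold and no allowance for frequency of contact, and it does not say which groups are compared.

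**Contact, STEEP-b.** Under Intervention: STEEP-b, "Adolescent mothers are visited at home every 2 to 3 weeks by the same adviser for 9 months". The programme is "completed in 12 to 18 sessions", and "an optional group meeting is offered every second month that mothers can attend".

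**Contact, both arms.** Under Measurement time points, assessments after baseline are "at the end of the 9-month intervention (T2, postintervention) and 6 months postintervention (T3, follow-up"). For TAU dyads these are the only post-baseline study contacts that the article describes.

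**The concern.** Three stated elements fit together badly: events count once they become known, one arm has far more study contact for nine months, and the board must act on a preponderance. Preponderance is a comparative word, and in a 1:1 two-arm trial a reader will naturally think of one arm against the other.

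If serious events have the same true rate in both arms, a STEEP-b event has many occasions to come to the study's notice within about three weeks. A TAU event that the mother does not volunteer waits for T2, and is missed if she leaves the study before then. Limiting the rule to possibly trial-related events does not clearly restore balance, because events in an arm with no added trial intervention are less likely to be linked to the trial.

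Two things are at stake. The board could read an ascertainment difference as harm. Or it could learn to discount STEEP-b excesses as surveillance, and so be slower to see a real one. The final harms table has the same weakness if TAU events are never recovered.

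**Working it through.** The article gives no SAE rate, recruitment pace or reporting fraction, so it has no figure of its own to reproduce. What follows is illustrative.

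**Contact before T2.** Nine months is 39.1 weeks. Visits every 3 or 2 weeks give 39.1/3 = 13.0 to 39.1/2 = 19.6, in line with the stated 12 to 18 sessions. TAU dyads have one post-baseline assessment in the same window.

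**Delay only, month 12.** Assumptions: uniform entry still under way, equal true rates, no drop-out, full recall at T2, STEEP-b events known at once. Exposure is in dyad-months per dyad entering each month, per arm.

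- Entered in months 0 to 3, already at T2: 3 × 9 = 27.
- Entered in months 3 to 12, not yet at T2: 9 × 9/2 = 40.5.
- STEEP-b known exposure: 27 + 40.5 = 67.5.
- TAU known exposure if a fraction s of events is self-reported before T2: 27 + s × 40.5.

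| s | TAU known | Ratio STEEP-b : TAU |
|---|---|---|
| 0 | 27 | 67.5/27 = 2.5 |
| 0.5 | 47.25 | 67.5/47.25 = 1.43 |
| 0.8 | 59.4 | 67.5/59.4 = 1.14 |

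The ratio does not depend on the SAE rate or, while entry is uniform and ongoing, on the speed of recruitment.

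**Same model with visits every 2.5 weeks in STEEP-b.** Self-reporting between visits has the same fraction s in both arms. The known share of true events at week 52, STEEP-b against TAU, is:

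- s = 0: 0.962/0.398 = 2.42
- s = 0.5: 0.981/0.699 = 1.40
- s = 0.8: 0.992/0.880 = 1.13

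For s = 0, 0.5 and 0.8, the ratios are 1.47, 1.19 and 1.07 at week 78, and 1.28, 1.12 and 1.05 at week 104. They return to 1.0 once every dyad has passed T2. Before any TAU dyad reaches T2, s = 0 means no TAU event is known at all, but that only restates the assumption.

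**Loss with drop-out, final table.** Let a fraction d of each arm leave before T2, evenly over nine months, with no TAU self-report. STEEP-b events are known up to departure, and TAU events of leavers are lost. For events before T2:

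ratio = [(1 − d) × 9 + d × 4.5] / [(1 − d) × 9] = 1 + d / [2(1 − d)]

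The article expects about 30 % drop-out over the whole study, which lasts 15 months per dyad (9 + 6).

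- Even loss over 15 months gives d = 0.30 × 9/15 = 0.18, and a ratio of 1 + 0.18/1.64 = 1.11.
- All loss before T2 gives d = 0.30, and a ratio of 1 + 0.30/1.40 = 1.21.

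**Loss through forgetting or non-report.** If 95 % of STEEP-b events and 80, 60 or 40 % of TAU events are ever recorded, the ratio is 0.95/0.80 = 1.19, 0.95/0.60 = 1.58 or 0.95/0.40 = 2.37. With equal detection it is 1.0.

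**The case against.** A reader might infer that a STEEP-b excess is bound to appear and that the rule will stop the trial falsely. The documents do not support that, for these reasons.

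- **The rule is not a raw count by arm.** It names no test and no significance level. It is confined to SAEs possibly caused by the trial, and an independent board of two clinical experts and a biometrician oversees the trial and can weigh unequal contact. Any false-stop probability needs a test that the reader supplies. With a one-sided exact binomial test at 0.025, 90 dyads per arm, 9-month SAE rates of 5 to 20 % and TAU detection of 80 to 40 % against 95 %, the probability of a significant STEEP-b excess runs from 1.7 % to 44 %. With equal detection it is 1.0 to 1.6 %. So wide a range shows that the inputs are unknown, and gives no estimate for this trial.
- **TAU mothers can report at any time.** The capture wording covers both arms. Nothing says that TAU events are learned of only at T2 and T3, or that advisers collect SAEs at home visits. Concomitant care is documented at every time point, which gives a retrospective route in both arms.
- **Delay alone corrects itself.** With full recall and retention the ratio is 1.0 once all dyads pass T2, and after T2 the described study contact is the same in both arms.
- **Detail may lie elsewhere.** The full protocol, the standard operating procedures or a board charter may set out SAE collection. Its absence from an article is not in itself a fault.

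All of this stands and limits the claim. It does not remove the point: capture on becoming known, unequal contact and a comparative trigger are all stated in the article, and the board needs comparable counts in order to use its judgement.

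**Conclusion.** The point holds as a risk of ascertainment bias. At equal true rates, unequal contact can make known SAEs more numerous and earlier in STEEP-b. At about month 12 the ratio is 2.4 to 2.5 if no TAU event is reported before T2, and falls to about 1.4 and 1.1 with 50 % and 80 % self-report. In the final table it is 1.0 with full recall and retention. It is about 1.1 to 1.2 for pre-T2 events if drop-out is the only loss and no TAU event is self-reported, and larger if TAU events are also forgotten.

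These ratios rest on equal true rates, uniform entry and home visits that do bring events to light. The article gives none of the three. Neither a certain excess nor a particular false-stop rate follows from it. The primary analysis is not affected. The change is worth making because it is cheap and both visits already exist.

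**What to change.** In Safety and ethical issues:

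1. Add one short structured SAE/AE question list with onset dates, identical in both arms, at T2 and T3. Ask it after the outcome assessments, so that an answer revealing allocation cannot affect a blinded assessor.
2. Flag each event by how it was found: home visit, self-report between visits, structured question, or other.
3. Give the board and the final report, alongside all known SAEs and not instead of them, a by-arm comparison limited to dyads that have reached the same visit and to events elicited there.

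Leave the 24 h reporting and the board's authority to terminate unchanged. Do not withhold SAEs found at home visits from any count, since that could delay a true signal by up to about nine months.

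The cost is one CRF page at two existing visits, a source field and one extra table. The like-for-like comparison becomes available later than the raw counts, and it cannot recover events in dyads lost before T2, so drop-out by arm should be shown beside it.

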## Discussion

Given the high prevalence of mothers with a history of abuse who maltreat their own children, a better understanding of this intergenerational transmission along with effective interventions to stop this cycle of violence are needed. Thus, there is an urgent need to study the effectiveness of early interventions to improve parental child-rearing attitudes and practices, particularly in at-risk mothers. The main aim of the current study was therefore to investigate within a randomized controlled trial the effects of a home-visiting mother-child intervention program (STEEP-b) plus psychiatric treatment of the mother when mental illness is present compared with TAU (treatment as usual, that is, standardized support from the child welfare system) on maternal sensitivity, child responsiveness, attachment and child development in adolescent, high-risk mothers. Adolescent mothers are a high-risk group for neglecting and abusing their children. Unfortunately, high-risk, adolescent mothers frequently do not participate in traditional intervention programs [26]. Therefore, Erickson and Egeland [35] developed a home-visiting program (STEEP) for young mothers with a focus on maternal sensitivity, a key factor in shaping attachment development and reducing child maltreatment [11–13, 25]. In the current study, this intervention program was adapted (STEEP-b) to improve treatment effectiveness. To this end, the intervention was modularized to enhance treatment integrity [36] with a clear behavioral focus on enhancing maternal sensitivity and reducing harsh parenting behaviors, which may be more effective in shaping attachment security and organization and thereby improving children’s development [25, 29]. Furthermore, the intervention was designed to be relatively brief (12 to 18 sessions) and started when the children are between 3 and 6 months old because a meta-analysis has shown that less, but intensive intervention sessions with an older infant are more effective [25]. In addition, a larger number of adolescent mothers might agree to participate in less frequent, compared with longer, interventions.

Based on the beneficial effects of STEEP on mothers’ parenting styles using a non-randomized design, STEEP is now included in the German “Communities that Care” database as a prevention program with probable empirical evidence. However, to date, no RCT on STEEP has been published, and one is therefore urgently needed.

In the current study, we will be able to investigate behavioral and neurobiological correlates of maternal sensitivity and the impacts of maternal behaviors on a child’s well-being in adolescent and adult mothers. We predict that the intervention will not only improve maternal sensitivity but will also improve a child’s responsiveness to their mother, attachment security, attachment organization and child development. If the current intervention program is successful, the findings will have important implications for community services and clinical work.

## Trial status

Mother-child dyads began to enter the trial in October 2012. Recruitment is still open.

## Abbreviations

BIS-15: Barratt Impulsiveness Scale
BITSEA: Brief Infant-Toddler Social and Emotional Assessment
BDI-II: Becks Depression Inventory, Second Edition
BSI-18: Brief Symptom Inventory
BSID-III: Bayley Scales of Infant and Toddler Development
CAARS: Conners Adult ADHD Rating Scale
CAPI: Child Abuse Potential Inventory
CECA-Q: Childhood Experiences of Care Abuse Questionnaire
CFT 20-R: Culture Fair Intelligence Test - Scale 2, Revision
ECBQ: Early Childhood Behavior Questionnaire
ECR-R: Experiences in Close Relationships Scale-Revised
EMBU: A questionnaire measuring perceptions of parental rearing behaviors
DERS: Difficulties in Emotion Regulation Scale
IBQ-R: Infant Behavior Questionnaire
IRI: Interpersonal Reactivity Index
M.I.N.I: Mini-International Neuropsychiatric Interview
PSI: Parental Stress Index
SCID-II: Structured Clinical Interview for DSM-IV axis II personality disorders
SSP: Strange Situation Procedure
STAI: State-Trait Anxiety Inventory
VASQ: Vulnerable Attachment Style Questionnaire
